## Abstract

**Background:**

Worldwide, opioid use causes more than 100,000 overdose deaths annually. Naloxone has proven efficacy in reversing opioid overdoses and is approved as an emergency antidote to opioid overdose. Take home naloxone (THN) programmes have been introduced to provide ‘community members’, who are likely to observe opioid overdoses, with naloxone kits and train them to recognise an overdose and administer naloxone. The acceptability and feasibility of THN programmes has been demonstrated, but the real-life effectiveness of naloxone administration by community members is not known. In recent years, the approval of several concentrated naloxone nasal-spray formulations (in addition to injectable formulations, eg.prenoxad) potentially increases acceptability and scope for wider provision. This study aims to determine the effectiveness of THN (all formulations) in real-world conditions.

**Methods:**

A European, multi-country, prospective cohort study, to assess the use of THN by community members to reverse opioid overdoses in a six-month, follow-up period. Participants provided with THN from participating harm reduction and drug treatment sites will be recruited to the study and followed-up for six months. We are particularly interested in the experiences of community members who have been provided with THN and have witnessed an opioid overdose. All participants who witness an opioid overdose during the six-month period (target approx. 600) will be asked to take part in a structured interview about this event. Of these, 60 will be invited to participate in a qualitative interview. A Post Authorisation Efficacy Study (PAES) for the concentrated nasal naloxone, Nyxoid, has been integrated into the study design.

**Discussion:**

There are many challenges involved in evaluating the real-life effectiveness of THN. It is not possible to use a randomised trial design, recruitment of community members provided with THN will depend upon recruitment sites distributing THN kits, and the type of THN received by participants will depend on regulations and on local clinical and policy decision-makers. Following up this population, some of whom may be itinerant, over the 6-month study period will be challenging, but we plan to maintain contact with participants through regular text message reminders and staff contact.

**Trial registration:**

ClinicalTrials.gov Identifier: NCT05072249. Date of Registration: 8.10.2021

**Supplementary Information:**

The online version contains supplementary material available at 10.1186/s12889-023-16445-6.

## Background

Opioid use is a global public health issue, causing more than 100,000 overdose deaths annually [1–4]. In Europe, 5,141 overdose deaths involving illicit drugs were reported in 2019, primarily from opioids [5]. In 2019, the mortality rate due to overdose was estimated at 14.8 deaths per million of the adult population in Europe [5].

Naloxone is a µ-opioid receptor antagonist which can reverse the respiratory depression effects of opioids by blocking receptors. It is approved as a clinical antidote to opioid overdose [6, 7]. Naloxone rapidly reverses the acute effects of opioids (e.g., heroin, fentanyl, methadone, buprenorphine, codeine, morphine, tramadol, and oxycodone) including extreme drowsiness, slowed breathing, and loss of consciousness, thereby having ability to prevent opioid overdose fatality.

Naloxone has been used since the 1970s to treat opioid overdose in hospital and pre-hospital settings [1, 8]. It has proven to be safe and effective when administered in time and at the right dose [7, 9]. Since the late 1990s, take home naloxone (THN) programmes have been introduced [10, 11]. Such programmes provide ‘community members’ who are likely to observe opioid overdoses (including people who use opioids themselves, their family, and carers) with naloxone kits and train them to recognise an overdose, call an ambulance, administer naloxone and perform basic life support [1].

Naloxone has proven efficacy and can be administered by the intravenous (IV), intramuscular (IM), subcutaneous (SC) or intranasal (IN) routes [7, 12–14] and the acceptability and feasibility of THN programmes have been demonstrated in many contexts [15–18]. A systematic review applying the Bradford Hill criteria to findings from existing non-randomized studies, found that THN programmes have led to improved survival rates among programme participants and reduced heroin overdose mortality rates in the community [19]. However, the real-life effectiveness of naloxone administration by community members in reversing opioid overdose is unknown. Conducting a randomised controlled trial in this setting would not be ethical. This study will be undertaken at a time of change for THN programmes in Europe, as new concentrated naloxone nasal-spray formulations have become available, sometimes alongside pre-filled syringes of injectable naloxone which have previously been offered through these programmes. All types of THN formulations will be examined in this study.^1^

This study aims to determine the effectiveness of THN in real world conditions. Study objectives include, assessing the rate of administration of naloxone and subsequent reversal of opioid overdose by community members who witness an opioid overdose, determining how closely real-life use conforms to overdose response training and obtaining a better understanding of naloxone administration and related overdose reversals by community members.

## Methods/design

### Study design and setting

This is a mixed-method, prospective, cohort study, to assess the effectiveness of naloxone administration and overdose reversal by community members across a number of European countries.

Quantitative data collection alone in the form of structured interviews cannot adequately capture the many interconnecting social, economic, and cultural factors that influence response to opioid overdose as well as the outcomes of such intervention. Therefore, a mixed methods approach, incorporating qualitative interview data, was selected for this study. The protocol was designed after discussions with people who use heroin and other opioids and who have been provided with take home naloxone. We consulted with various communities of service users with living and lived experience, including patients in opioid treatment, individuals currently using opioids and at risk of overdose, individuals in recovery, and commissioners and provider organisations. They told us that overdose is of major concern, that they would be happy to answer questions about their experience of witnessing an overdose and administering naloxone (or not) and advised on the timings and content of the interviews.

Due to COVID-19 social distancing restrictions before July 2021, the study includes methods that allow for enrolment and follow-up interviews to be carried out remotely.

Participants, provided with THN from participating harm reduction and drug treatment sites, will be recruited and followed-up for six-months (Total cohort). All participants who witness an opioid overdose during the six-month period will be asked to participate in a structured interview about this event (Witnessed overdose cohort). In addition, there are two nested sub-studies. Sub-study A comprises two structured surveys, to assess the concentrated naloxone nasal-spray formulation training materials. Sub-study B comprises qualitative interviews conducted with a sample of those who have witnessed an opioid overdose and undertaken a structured interview to better understand the use, safety, and effectiveness of different naloxone products (Fig. 1). A Post Authorisation Efficacy Study (PAES) for the concentrated nasal naloxone, Nyxoid, has been integrated into the study design.

**Fig. 1 Fig1:**
[figure not shown]
Consort flow diagram

Conducting the study in multiple European Economic Area (EEA) countries will increase the generalisability of findings across Europe. There are various medical, treatment, cultural and health care system related factors and drug use and treatment approaches which differ across European countries. Due to these factors, the introduction of naloxone programmes, and the forms of naloxone provided (e.g., concentrated naloxone nasal spray or pre-filled syringes of injectable naloxone) are not evenly distributed over EEA countries.

The study will be undertaken across several European countries. Participating countries will be chosen based on, whether they report high rates of opioid use and fatal overdoses, and provision of THN: they are thus likely to be countries with the highest rates of drug-induced mortality in Europe [5]. We anticipate that they will provide an approximate estimated equal split between those providing nasal and injectable forms of naloxone.

Countries need to be able to recruit the target number of participants and for such participants to be contactable for follow-up (particularly the expected 10% who will witness an opioid overdose within the study period).

Within each country, recruitment sites will need to fulfil the following criteria:routinely provide THNbe an active drug treatment facility, needle and syringe programmes (NSP) or community/family support group for people who use opioidscan reasonably commit to recruit a substantial number of people that (combined with the other sites in the country) can reach the country target of 1,000 participants

### Study population

Individuals provided with THN from participating harm reduction and treatment sites in each of the countries will be recruited to the study. Participants receiving THN (reflecting usual clinical practice of providing THN to community members who are likely to observe an opioid overdose) will include the following groups:individuals with an opioid use disorder and in contact with treatment servicesindividuals with an opioid use disorder and out of contact with treatment services, but in contact with harm reduction services (e.g., NSP schemes, supervised consumption facilities and outreach)family members and carers of individuals with an opioid use disorderhealth /social care staff (not including medically trained health care professionals)

We do not seek to influence the prescribing activity of the services, and so we are not seeking to influence the proportions in each group to whom THN is provided. However, based on observations of recent clinical practice, we consider that it is likely that participants will be recruited mostly from eligibility groups a) and b).

Inclusion criteria will include:Member of one of the groups above (a-d)Aged ≥ 18 yearsProvided with THN supply at time of enrolment (or can demonstrate that they have a supply of THN (in-date) and have received training at time of enrolment)Have access to reliable mobile telephone and can present it at the point of enrolmentWilling to participate in study follow-upProvided verbal or written informed consent

Exclusion criteria will include:Needs an interpreterAlready entered the studyNot willing or able to partake in follow-up phone survey

Between June 2021 and April 2024, we intend to recruit the total cohort of 6,000 participants, including approx. 3,000 participants supplied with concentrated naloxone nasal spray and 3,000 with pre-filled syringes of injectable naloxone. With each country recruiting approximately 1,000 participants.

However, our main interest is in recruiting our witnessed overdose cohort of approximately 600 participants, including approximately 300 provided with the concentrated naloxone nasal-spray. These study participants will include those who have witnessed an opioid overdose in the 6-month study period (and completed a structured interview). Of these, 60 participants from England, Scotland, or Wales, will also participate in a longer, in-depth qualitative interview conducted by telephone (Sub-study B). We focus on collecting data on one witnessed overdose per participant.

### Objectives and outcome

#### Main study objectives

There are two co-primary objectives:To determine the frequency of deaths in the 24 h (or later if information is available) subsequent to administration of naloxone by community members, to reverse an opioid overdose in real world settings.To determine the proportion of naloxone administration with the intention of reversing an opioid overdose by community members provided with THN who witness an opioid overdose.

Secondary objectives include:aDaily carriage rate of THN amongst community members supplied with THN over a 6-month periodbProportion of community members supplied with THN who witness an opioid overdose over a 6- month periodcProportion of community members supplied with THN who witness an opioid overdose, where there is THN presentdProportion of community members supplied with THN, who witness an opioid overdose, where there is THN present and who administer THN to reverse an opioid overdoseeProportion of community members who report a recurrence of respiratory depression in a person who has been administered THN for an opioid overdose within 1-h of THN administrationfProportion of community members who report a second dose of naloxone administered to a person experiencing an opioid overdose within 1-h of administration of the first dose of THNgProportion of community members who report opioid withdrawal symptoms and/or angry (including abusive or hostile) reaction precipitated when THN is administered for the reversal of an opioid overdosehSurvival rate of individuals having received naloxone at 2 h post—administration of THN or at arrival of ambulance/medical assistance if this occurs before 2 h have passed since the THN was administered, as far as this can be ascertainediProportion of fatal outcomes within a 12-h period after the witnessed opioid overdose, as far as this can be ascertainedjIn case of fatal outcome: what is known about the cause of the fatal outcome (other than fatal overdose), based on any direct or second-hand information available to the participant (e.g., delays in delivery of intervention such that death or irreversible brain damage already occurred, and/or failures by the responder such as failure to call emergency services or failure to administer naloxone, and/or failure of the naloxone to reverse the overdose, and/or failure of the medication device)kAccuracy of diagnosis of a probable opioid overdose by community memberlAppropriateness of response to opioid overdose by community membermExplore the use, safety, and effectiveness of different naloxone productsnPercentage of participants, who are at a risk of experiencing an opioid overdose themselves, who report experiencing an opioid overdose (fatal or non-fatal) during the study period

#### Sub-study A

Objectives include the extent to which the participant read, understood, and followed the concentrated naloxone nasal-spray instructions.

#### Sub-study B

Objectives include, providing more detailed insights into a witnessed overdose situation.

#### Main study outcomes

Co-primary outcomes (of witnessed overdose cohort) include:

Among community members provided with a supply of THN and witnessing an opioid overdose, a) the proportion administering THN to reverse an opioid overdose, and the frequency of deaths within 24-h (or later if information is available) after administration of THN. Overdose events eligible for inclusion in the primary outcome analysis are opioid overdoses witnessed by the participant during the six-month period after study enrolment.

Secondary outcomes include:

Of the Total cohortPercentage of participants who report carrying THN (on day of interview)Percentage of participants who witness an opioid overdose over 6-month periodPercentage of participants, who are at a risk of experiencing an opioid overdose themselves, who report experiencing an opioid overdose (fatal or non-fatal)”

Of the Witnessed overdose cohort:Percentage of participants who are carrying THNPercentage of participants who report there was THN presentPercentage of participants who state there was THN present, and administer THNPercentage of participants who administer THN and report that respiratory depression occurred in the person they resuscitated within one hour of THN administrationPercentage of participants who report administering a second dose of THN to a person experiencing an opioid overdose, within 1-h post administration of first dose of THNPercentage of participants who report that withdrawal symptoms and/ or anger, rage or violence occurred in person they resuscitated with THN. Frequency of each symptom witnessed (at most recent overdose witnessed)Percentage of participants who report that the person receiving naloxone has survived at 2 h post administration of naloxone, OR at arrival of ambulance/medical assistance, if this occurs before 2 h have passed since the opioid overdosePercentage of participants who report fatal outcomes within 2 h of the identification of opioid overdose, or at the arrival of an ambulance/medical assistance, where THN was administered and where THN was not administeredPercentage of participants who correctly diagnose opioid overdose crisis (assessed through multiple response questions)

Data on wider response to the overdose, in addition to naloxone, will be collected. This will include: tried to wake them verbally (shouted/ called the person’s name), tilted head back, checked for response, checked breathing, put into recovery position, chest compressions, rescue breathing / mouth-to-mouth, cleared airways, checked pulse, ambulance called, ambulance gave naloxone.

Data will be captured through a structured questionnaire developed specifically for this study (See Supplementary information: Questionnaire). The questionnaire was informed by literature reviews, clinical guidelines, previous research undertaken by the authors, and consultations with service users with living and lived experience. It was piloted before the study started. The main observation window has been limited to one hour because, death from an opioid overdose is likely to be within minutes to hours and medical care is expected to have been handed over to medical practitioners (e.g., paramedics, ambulance personnel, etc.) within this time-period. The potential resuscitating effects of naloxone are also effective within a short period (minutes) and of limited duration (minutes to hours; assuming that naloxone has been administered at a time when no irreversible damage has occurred). Deaths occurring outside of the 1-h time window may be indirectly related to the overdose (e.g., aspiration pneumonia, anoxic brain trauma, multiorgan failure due to rhabdomyolysis) and because of either zero or late interventions. They would not be caused by a failure of naloxone to acutely treat the respiratory depression due to opioid overdose. Moreover, participants may not know the opioid overdose patient sufficiently and may be unlikely to be able to provide longer term follow-up information. However, because of possible delays in pronouncing death, a 2-h time limit will be used as far as it can be ascertained.

*Sub-study A outcomes:*

Of the Total cohort:Percentage of participants who received various forms of training materials during their naloxone training

Of the Witnessed overdose cohort:Percentage of participants who appropriately recognised and responded to an overdose

*Sub-study B outcomes:*
Increased understanding of carriage of naloxone products and disposal of used kitsIncreased understanding of how naloxone is administered in an emergency overdose situation, including any problems encountered (e.g., device malfunction or misuse)Increased understanding of decision-making processes relating to naloxone administration in an emergency opioid overdose situation, including giving/not giving a second doseIncreased understanding of the impact of the social and environmental setting in which the overdose occurs – on naloxone useIncreased understanding of the links between naloxone carriage and use on willingness to call an ambulance when witnessing an opioid overdoseIncreased understanding of the effectiveness of naloxone administration, including speed of reversal and opioid overdose outcomeIncreased understanding of any negative consequences of naloxone administration (e.g. withdrawals, aggression, respiratory depression and death by the person who experienced the overdose) and their implications for future opioid overdose events witnessedIncreased understanding of care of the person who experienced the overdose both during the opioid overdose and post-naloxone administrationIncreased understanding of knowledge of naloxone, including training and information needsIncreased understanding of views on the THN training materials

In addition, the clinician assessment will establish:
Accurate diagnosis of opioid overdose (5-point Likert scale) through expert assessment of transcriptsAccurate identification of respiratory depression (5-point Likert scale), through expert assessment of transcriptsAppropriate response to opioid overdose (5-point Likert scale) through expert assessment of transcriptsAdequate post naloxone aftercare (5-point Likert scale) through expert assessment of transcripts

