### Study analysis

The rate of administration of THN by community members witnessing an opioid overdose and the frequency of deaths in the 24 h (or later if information is available) after administration of naloxone will be estimated as proportions. The study data will be stratified by participant groups as follows: 1) Patients in treatment for opioid use disorder (OUD), 2) Participants who use opioids but are not currently in treatment, 3) Friends and family members, 4) Staff working with individuals with OUD. Effective administration rates of THN by community members will be estimated as proportions. The outcomes will also be estimated for each THN formulation (including the multiple intranasal and injectable formulations that will be captured in this study).

All secondary and exploratory endpoints will be estimated as proportions. Demographic and clinical characteristic data for study participants will be reported using summary statistics for continuous variables (means and standard deviations or medians and interquartile ranges) or frequencies and percentages for categorical variables, as appropriate.

Descriptive data will be reported as numeric counts and percentages with the denominator for reporting percentages appropriate to the specific question.

The extent of missing data at each quantitative study inquiry stage will be tabulated appropriately.

The key population under investigation will be those included in the witnessed overdose cohort (~600). It is anticipated that this will only have missing item level data, as by being in the witnessed overdose cohort, they will be followed up. We do not anticipate any additional analyses in those lost to follow up between those initially enrolled (~6,000) and those included in the witnessed overdose cohort primary population (n ~ 600). We are monitoring the event rate within those initially enrolled as it could be the case, that we could stop enrolment sooner than anticipated, if the event rate is considerably higher than initially estimated.

Planned subgroup analysis will include the following: type of participant (e.g., participant witnessed an opioid overdose event, or experienced an opioid overdose event), age of participant, sex of participant, THN formulation, and carrier of THN versus non-carrier.

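### The mortality co-primary has no fixed time horizon, so its proportion rests on unequal, information-dependent follow-up of the casualty

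*Protocol article*

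**What the plan says.** The mortality co-primary appears three times in the protocol article, each time with the same open end.

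- Main study objectives: "frequency of deaths in the 24 h (or later if information is available) subsequent to administration of naloxone".
- Main study outcomes: "the frequency of deaths within 24-h (or later if information is available) after administration of THN".
- Study analysis: "or later if information is available) after administration of naloxone will be estimated as proportions".

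Main study outcomes also contains a rationale for observation windows. It states that "The main observation window has been limited to one hour" and says of deaths beyond that hour: "They would not be caused by a failure of naloxone to acutely treat the respiratory depression due to opioid overdose". It adds that "participants may not know the opioid overdose patient sufficiently and may be unlikely to be able to provide longer term follow-up information", and concludes that "because of possible delays in pronouncing death, a 2-h time limit will be used as far as it can be ascertained".

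The secondary fatality measure has two windows. Objective (i) refers to "fatal outcomes within a 12-h period after the witnessed opioid overdose". The corresponding item in the outcome list uses 2 h from identification of the overdose, or the arrival of an ambulance or medical help.

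On sources of information, Recruitment of participants and Mortality data describe death-register linkage for study participants who use drugs and are themselves at risk. Follow-up assessments describes an interview as soon as possible after a witnessed overdose, prompted by monthly texts and staff contact, with a structured call to everyone at six months.

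**The concern.** A proportion of deaths is interpretable when every person in the denominator has been observed over the same period, or when departures from that are visible. Here the stated rule sets 24 h but also admits any later death that happens to be known. Two casualties who both die several days after the event can be classified differently: one is counted because the witness is a relative or is interviewed at six months, and the other is not because the witness was a stranger or was interviewed the next day.

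This matters because the proportion is itself the result in a descriptive study, and because Study analysis plans to report outcomes by participant group and by naloxone formulation. Groups that differ in how well they know the casualty, or in how promptly they are interviewed, could show different mortality with no difference in risk. The protocol's own rationale for short windows does not say why this endpoint should run to 24 h or beyond.

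**Working it through.** **1. The plan's own figures.** From the sample-size section on mortality: assumed rate 1.4%, 600 witnessed overdoses, about 8 deaths, 95% confidence interval within ±1.5%.

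- Expected deaths: 600 × 0.014 = 8.4, which agrees with the stated figure.
- Wald half-width: 1.96 × √(0.014 × 0.986 / 600) = 0.0094, or ±0.94 percentage points. The exact (Clopper-Pearson) interval for 8/600 is 0.58% to 2.61%. Both lie within ±1.5%.

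No stated number is wrong. However, the 1.4% is not attached to any time horizon, so it does not settle which window was intended.

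**2. The horizons side by side.**

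| Place | Quantity | Horizon |
|---|---|---|
| Objective, outcome and analysis of the co-primary | Deaths after naloxone | 24 h, then open-ended |
| Rationale in Main study outcomes | Main observation window | 1 h |
| Same rationale | Limit for death | 2 h |
| Secondary objective (i) | Fatal outcomes | 12 h |
| Matching secondary outcome | Fatal outcomes | 2 h or ambulance arrival |

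Different horizons for different endpoints are acceptable. Two things are not: the first row has no upper limit, and the last two rows give different windows for what appears to be one measure.

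**3. Where information on later deaths can come from.** Register linkage covers study participants, so it does not supply the casualty's vital status. That leaves the witness's report. Its reach depends on acquaintance with the casualty, which the protocol says may be insufficient, and on the interval from event to interview. That interval can be very short, or can approach six months for an overdose early in follow-up that is first reported at the final call.

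**4. Size, by illustration only.** The documents give no risk of death beyond 24 h and no share of witnesses with later information. Assume 1.4% is the 24-h risk, let d be the added later risk, and let f be the share of events with later information. The expected estimate is then

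estimate = 1.4% + f × d.

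| d (percentage points) | f = 0 | f = 0.25 | f = 0.5 | f = 0.75 | f = 1 |
|---|---|---|---|---|---|
| 0.2 | 1.40% | 1.45% | 1.50% | 1.55% | 1.60% |
| 0.5 | 1.40% | 1.525% | 1.65% | 1.775% | 1.90% |
| 1.0 | 1.40% | 1.65% | 1.90% | 2.15% | 2.40% |

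At n = 600 the expected deaths rise from 8.4 at f = 0 to 9.6, 11.4 or 14.4 at f = 1. Two strata with identical risk but f = 0.25 and f = 0.75 would differ by 0.5 × d, that is by 0.1, 0.25 or 0.5 percentage points. For scale, the sampling half-width for the whole cohort is 0.94 points, so most of these shifts are smaller than the random error. Unlike random error, they do not shrink with sample size and the confidence interval does not show them.

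With the window closed at 24 h, the term f × d disappears.

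**The case against.** The strongest reply is that the co-primary is a count of all deaths after administration and is not defined as naloxone failure. Counting a later death therefore does not conflict with saying that such a death would not be a failure of naloxone. The plan also has separate 2-h survival and 2-h fatality outcomes, and the 2-h limit in the rationale matches them. That much stands. A reader might infer that the rationale flatly contradicts the co-primary, but the text can be read as supporting the 2-h secondary outcomes. It does not say so, which is a reason to clarify. A fixed 24-h window would not remove that tension either, since deaths between 2 h and 24 h would still count.

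A reader might also infer a large distortion from casualties whose 24-h status is unknown. If 10% to 20% were unknown and 1.4% of the known had died, treating all unknowns as alive gives 1.4% × (1 − u) = 1.26% to 1.12%. Treating all as dead adds u, giving 11.26% to 21.12%. Those shares are assumptions without support in the protocol, and the ranges come from missing status at 24 h, so removing the open end would not change them. Coding of unknowns may sit in the analysis plan or the questionnaire, neither of which is shown, and Study analysis does promise to tabulate missing data.

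It is also tempting to say that so few deaths are expected that one late death moves the estimate by a fifth or more. That takes 6% to 63% of 600 as treated (36 to 378 events), hence 0.5 to 5.3 deaths at 1.4%, which is a separate question about the denominator. At the plan's own 8.4 deaths, one extra death is a relative change of about 12% (1/8.4), or 0.17 percentage points (1/600).

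Finally, the study is descriptive with no inferential tests, and most participants are expected to be people with opioid use disorder, so contrasts with family members or staff concern the smaller strata. This limits the consequence without giving the endpoint a horizon.

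**Conclusion.** The point holds as a defect in the definition of a co-primary endpoint: no upper time limit, reliance on the witness for later deaths, and interview timing that varies by up to about six months. The proportion can therefore differ between groups or formulations through ascertainment alone. Its size cannot be derived from the documents. Under the illustrative late risks of 0.2 to 1.0 points, the overall estimate could lie anywhere from 1.4% to 1.6%, 1.9% or 2.4% depending only on the information available. The mismatch between 12 h and 2 h in secondary objective (i) and its outcome holds on the text and needs no assumption.

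The documents do not show a material bias, do not refute any stated figure, and do not establish that unknowns will be mishandled. This is something that should be fixed; it does not invalidate the study.

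**What to change.** 1. Delete the bracketed extension beyond 24 h from the objective, the outcome and the analysis text. Count only deaths within a fixed 24 h of administration in the co-primary, and list later deaths descriptively with time since the event where known.
2. Report the number of casualties with unknown 24-h status beside the estimate, overall and by participant group and formulation. As a sensitivity display, add bounds with all unknowns alive and all unknowns dead.
3. State which outcomes the 1-h and 2-h rationale in Main study outcomes applies to, and why the co-primary uses 24 h.
4. Give secondary objective (i) and its outcome the same window; the 12-h and 2-h texts must be reconciled.

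The cost is a few wording changes and one extra table, plus a response category for unknown status if the questionnaire lacks one. The small downside is that later deaths leave the co-primary and are reported separately.
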